### Intervention

The intervention will consist of the use of a decision aid (*Statin Choice* and *Aspirin Choice,* or *Diabetes Medication Choice*) by patients and their primary care clinician during the clinical encounter (http://kercards.e-bm.info).

#### Decision aids

The *Statin Choice* decision aid has three different versions according to baseline 10-year cardiovascular risk, pre-assessed for each patient: 10% (used for patients with a 10-year cardiovascular risk <15%), 20% (for patients with estimated risk between 15 and 30%), and 50% (for patients with estimated risk >30%) [6,11]. The decision aid also presents the absolute risk reduction of cardiovascular events with statins, the potential downsides of taking statins, and a question prompting patients to express whether they are ready or not to make a decision and consequently which action they would like to take. The *Aspirin Choice* decision aid is similar to the *Statin Choice* decision aid with the only difference being that it presents the absolute risk reduction of cardiovascular events with aspirin. The *Diabetes Medication Choice* decision aid takes the form of cards that compare commonly used diabetes medication classes across several domains (e.g., reduction in HbA1c, weight gain, cost, mode of administration) that patients with type 2 diabetes and clinicians consider important when choosing these medications [7,8].

#### Training of clinicians

A study team member will conduct a demonstration showing how to use the decision aid at the time of the initial in-person discussion with clinics. The focal points of the demonstration will be that decision aids serve as guides for conversation rather than scripted discussions; that clinicians have flexibility in the manner in which they use the decision aid, including how and when they use them during the visit; and that they may elect not to use the tools with certain enrolled patients, per their own judgment. Brief video clips and storyboards that demonstrate the basic use of decision aids are publicly available at http://kercards.e-bm.info for clinicians to review at their convenience. A study team member will remain available to do one-on-one demonstrations after the initial group demonstration if needed.

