### Participant recruitment

We will send an introductory letter providing an overview of the study and inquiring about potential interest to eligible practices. Study team members will then personally visit interested clinics to discuss the study in more detail with clinic leaders. We will identify a lead clinician (“clinical champion”) to become the contact person for each practice for the duration of the study and seek participation of clinicians during this first meeting when the study is discussed. Potentially eligible patients will be identified through the diabetes registry, and we will note their upcoming appointments with participating clinicians. A study team member will contact these patients in advance to seek their participation in the study. Trained study personnel will obtain written informed consent to participate in the study from both clinicians and patients prior to their clinical encounter.

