### Allocation procedures

Randomization will be by practice. The study will compare the use of the decision aids within the clinical encounter versus usual care. We will identify pairs of practices that are most similar in size (i.e., number of clinicians seeing adult patients with type 2 diabetes) and randomize within each pair to use either the 1) the *Statin Choice* and the *Aspirin Choice*, or 2) the *Diabetes Medication Choice* decision aid. Each practice will also serve as the usual care arm for the other intervention arm (Figure 2). This approach will seek to ensure similar representation of ‘easy’ and ‘difficult’ practices in both decision aid groups and eliminate the need for any site to simply serve as a usual care arm. A study statistician will perform the randomization centrally after the practices have been enrolled, ensuring concealment of allocation of the paired practices. Practices, clinicians, patients, and investigators will not be masked to the intervention. However, patients providing outcomes will remain masked to their practice status, as consent documents will keep patients unaware of the study’s main hypotheses. Furthermore, we will centrally follow patients and ensure that patient surveys and pharmacy follow-up are completed according to the intention-to-treat principle.

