### Usual care

For patients in the usual care arm, clinicians will manage the discussion about medication regimen as usual, without using decision aids.

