##### Sample size

A total of 8 practices will be randomized to 1) the Diabetes Medication Choice decision aid plus statin and aspirin usual care or 2) the Statin Choice and Aspirin Choice decision aids plus diabetes medication usual care. The Statin Choice cluster randomized trial evaluated decision quality comparing the decision aid to usual care. This study reported a 9.8 point difference in decision quality^3^ with the standard deviation of 16.9 and 14.1 for the usual care and decision aid groups, respectively. Making the following assumptions: 1) variances are as reported in this study; 2) we seek to detect a difference of 9.8 points or greater in decision quality between two groups at significance level of 0.05, with a two-sided *t*-test; 3) a modest correlation of outcomes across these clinicians and practices (which is a conservative assumption) represented by an intracluster correlation coefficient (ICC = between cluster variance/total variance) of 0.05; 4) a variance inflation or design effect factor [1+ (n − 1) · ICC], where n is the number of patients per cluster [31]; and 5) an approximated 20% attrition rate, we will have 80% power if we are able to recruit 30 patients per clinic for a total recruitment target of 240 patients. Assuming a similar ICC and attrition rate for other outcomes, this sample size will have 99% power to detect a 1 SD difference in any continuous measure (e.g., approximately a 2-point difference in a 10-question knowledge scale), and 80% power to detect a 30% difference in 6-month adherence rates assuming a control adherence rate of 50%. Actual power will be likely greater because we will adjust for baseline values and characteristics and because of our conservative assumptions.

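### As written, the decision aid demonstration is given before randomisation, so it cannot be limited to the tool a practice is assigned

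*Protocol article*

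**What the plan says.** Four sections of the protocol article bear on the order of events.

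- **Participant recruitment.** After an introductory letter, "Study team members will then personally visit interested clinics to discuss the study in more detail with clinic leaders". The team will also "seek participation of clinicians during this first meeting when the study is discussed".
- **Training of clinicians.** A team member will "conduct a demonstration showing how to use the decision aid at the time of the initial in-person discussion with clinics". One-on-one demonstrations are offered later if needed. The same section adds: "Brief video clips and storyboards that demonstrate the basic use of decision aids are publicly available".
- **Allocation procedures.** "A study statistician will perform the randomization centrally after the practices have been enrolled". Practices are paired by size and randomised within pairs to the statin and aspirin aids or to the diabetes medication aid. "Each practice will also serve as the usual care arm for the other intervention arm".
- **Usual care.** In that arm "clinicians will manage the discussion about medication regimen as usual, without using decision aids".

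No section says that the demonstration follows allocation, or that it covers only the assigned tool.

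**The concern.** Randomising whole practices normally keeps usual-care clinicians away from the intervention. Here every practice has both roles: it uses the aid for one topic and gives usual care for the other. The separation therefore depends on clinicians not being introduced to the aid for their usual-care topic. A demonstration held before allocation cannot ensure this, because nobody yet knows which tool a practice will receive.

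The primary outcome is decisional conflict, measured straight after the visit with a modified scale whose items concern the quality of deliberation (Outcomes measures). A clinician who has seen an aid may carry its content or structure into a usual-care discussion without having the aid in hand. That would improve the comparator and shrink the contrast. The sample size calculation makes no allowance for it.

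**Working it through.** **Order of events, from the text**

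1. The team visits interested clinics. These are not yet enrolled (Participant recruitment).
2. Clinicians' participation is sought at that meeting (Participant recruitment), and the aid is demonstrated at the initial in-person discussion (Training of clinicians).
3. Practices are enrolled.
4. The statistician randomises (Allocation procedures).

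The demonstration is in step 2 and the allocation in step 4.

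**Who is exposed**

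Training of clinicians refers to the aid in the singular and does not name it, so there are two cases.

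- All tools are shown: all 8 practices see the aid for their usual-care topic.
- One tool is shown: the practices later assigned to the other tool see the aid for their usual-care topic. With pairwise randomisation of 8 practices, that is 4.

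In either case some usual-care clinicians are exposed. Two readings would avoid this. Either allocation was already known, which contradicts Allocation procedures, or the demonstration was at a later meeting, which contradicts the wording of Training of clinicians.

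**The plan's own power figure**

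Inputs from Sample size: difference 9.8; SDs 16.9 and 14.1; two-sided 0.05; ICC 0.05; 20% attrition; 8 clinics of 30 patients.

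- SD = √((16.9² + 14.1²)/2) = 15.56
- Patients per arm after attrition = 120 × 0.8 = 96
- Design effect = 1 + (30 − 1) × 0.05 = 2.45
- Effective n per arm = 96/2.45 = 39.2
- Standard error = 15.56 × √(2/39.2) = 3.52
- Power = Φ(9.8/3.52 − 1.96) = 79.6%

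This reproduces the stated 80%. With 24 completers per clinic in the design effect instead (2.15; effective n 44.7), power is 84.5%.

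**Illustration of dilution**

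Suppose content spill-over without use of the aid removes a fraction c of the difference, with the SD unchanged. The difference becomes 9.8 × (1 − c). The values of c are assumptions; the documents give none.

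| c | Difference | Power, design effect 2.45 | Power, design effect 2.15 |
|---|---|---|---|
| 0 | 9.8 | 79.6% | 84.5% |
| 10% | 8.8 | 70.8% | 76.4% |
| 20% | 7.8 | 60.6% | 66.3% |
| 30% | 6.9 | 49.6% | 54.9% |

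These figures cover only spill-over without use of the tool. Under Analysis (Aim 1), a patient whose encounter actually uses an aid is grouped in the decision aid arm, so such use would not act through the factor 1 − c.

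**The case against.** The best defence is that a condensed article may have merged a recruitment visit with a later start-up session. Participant recruitment speaks of meeting clinic leaders, whereas Training of clinicians speaks of a group demonstration and mentions neither enrolment nor randomisation. That is possible, but nothing in the text says so. If practice differs, the text still needs correcting.

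A reader might infer that every practice receives hands-on training in its control tool. The document does not support that. It describes a demonstration, does not name the tool, and lists general focal points: the aid guides conversation, its use is flexible, and clinicians may decline to use it. Exposure of every practice follows only if all tools are shown.

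Three further objections stand in part.

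- Some exposure is built into the design. Clinicians learn the general approach from their own assigned tool, and the training material is public. Moving the demonstration removes only the added exposure to the other tool.
- Actual use of the other aid has practical limits. Statin Choice comes in versions matched to a pre-assessed risk, and Diabetes Medication Choice is a set of cards. A demonstration alone does not put these into a usual-care visit, and the plan says that such visits proceed without aids.
- The likely direction is toward no difference, in a study that the Abstract describes as giving a preliminary estimate. This limits the harm, but an estimate biased toward no difference is still a poor guide to later work.

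**Conclusion.** The point holds on the order of events. Read together, the sections put the demonstration before randomisation, so it cannot be restricted to the assigned tool, and at least some practices are shown the aid for which they serve as usual care. The likely consequence is a comparison biased toward no difference.

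The size of that bias cannot be derived from the documents. A reader might take the fall in power to about 71% to 50% as the trial's expected power. It is not: it rests on an assumed 10% to 30% dilution, and only through content carried over without use of an aid. The stated 80% is arithmetically sound on its own assumptions. Nor should the grouping of patients by actual aid use be counted as further weight here; that is a separate matter.

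The change is worth making because the added exposure is avoidable at little cost, not because a given loss has been shown.

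**What to change.** Amend Training of clinicians so that the first meeting gives only a study overview. State that the group demonstration and any one-on-one sessions follow randomisation and cover only the tool or tools assigned to that practice.

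Use the planned video review to report any use of an aid in usual-care encounters. Encounters are already videotaped, a fidelity checklist exists for each aid, and recordings from both arms are already to be analysed, so this adds mainly a reporting line.

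The cost is one postponed or extra session per practice, at most eight. The change does not remove exposure through the public website or through experience with the practice's own assigned tool. The report should name both as remaining sources of contamination.

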### Usual care

For patients in the usual care arm, clinicians will manage the discussion about medication regimen as usual, without using decision aids.

### Frameworks

The RE-AIM framework will guide this study (aim 1). This framework has been developed specifically to address how an intervention, in this case use of decision aids, is implemented in a real-world setting [12,13]. Dimensions of the RE-AIM include: *Reach* (how broadly is this intervention used within the practices), *Effectiveness* (what is the impact of the intervention on outcomes), *Adoption* (can this be adopted by new groups with ease and minimal modifications), *Implementation* (what are the special issues and barriers in implementation), and *Maintenance* (can the intervention be maintained and will the impact continue) [12,13]. To complement the RE-AIM framework, we will use the Normalization Process Theory (aim 2) [6,14]. This applied theoretical model focuses attention on the practical work that facilitates understanding of the factors that promote and inhibit the routine embedding of interventions, such as decision aids into practice, in a structured and parsimonious way. The combination of an established implementation framework and robust explanatory model will provide a strong foundation for process evaluation of the trial.

### Data collection & analysis

#### Aim 1. Evaluating the impact of patient decision aids

We will collect patients’ data through 1) self-reported questionnaires administered before and after the clinical encounter with their clinician, and at 3 and 6 months post encounter; and 2) information about diabetes-related care included in medical records. Participating clinicians will be given a brief questionnaire to complete immediately following each clinical encounter with a participating patient. In addition, we will videotape each clinical encounter. Practice data will be obtained from administrative and patient medical records.

##### Outcomes measures

To assess *Effectiveness* of the decision aids (R**E**-AIM) we will measure the decisional conflict as the primary outcome and patient involvement in decision making, diabetes care processes, medication adherence, glycemic and cardiovascular risk factor control, and resource utilization as secondary outcomes, in the following way:

· *Patients’ decisional conflict*. Patients will complete, immediately after the clinical encounter with their clinician, a modified version of the Decisional Conflict Scale [15], the most commonly used outcome measure in decision aid trials [5]. These modifications entail the use of brief items that explore the quality of the deliberation process during the visit. Psychometric properties include good internal consistency, test–retest reliability, and effect sizes for responsiveness to change ranging from 0.4 to 1.2 [15,16].

· *Patients’ involvement in decision making*. We will use the OPTION scale to assess the extent to which clinicians seek to engage patients in decision making [17,18]. OPTION is a third-person observer scale and was designed for use in reviewing audio recordings of primary care visits. Our group has extended the use of this tool to video recordings with excellent inter-rater reliability (intraclass correlation coefficient >0.7) [6,19,20].

· *Patients’ knowledge*. Patients will complete a knowledge questionnaire immediately following the encounter with their clinicians, and at 3 and 6 months post-encounter. The questionnaire was developed according to prior recommendations and is similar to questionnaires used in our previous studies, addressing general knowledge about diabetes and lipid management and specific information contained in the decision aids [6,8].

· *Patients’ satisfaction*. Satisfaction with decision making will be assessed using items from the Decisional Conflict Scale [15] as well as two specific questions that require patients to assess the extent to which they would want for themselves and recommend to others similar decision support as they received during the visit. Other questionnaires exist to specifically address this domain, but our use of the Decisional Conflict Scale for this purpose reflects our effort to minimize participant burden.

· *Patients’ quality of life*. Patients will assess their health-related quality of life prior to the clinical encounter through the use of the EuroQol EQ-5D scale in which they list their health as excellent, very good, good, fair or poor [21]. The EQ-5D has been used in primary care [22,23] and in diabetes care and diabetes trials [24,25].

· *Patients’ hemoglobin A1c, lipids, blood pressure, & body mass index.* Medical records will be the source of information about these commonly used intermediate outcome measures for diabetes [26,27].

· *Patients’ prescription drugs.* Prescription drug and billing data will be collected through pharmacy records. Patients will be asked to provide written authorization to contact their pharmacy and release this information to the investigators. We have been able to obtain complete pharmacy records for all of our participants in previous trials [6,8].

· *Patients’ adherence*. Adherence and persistence measures will be derived from patient self-report, metabolic outcomes (indirect measure), and pharmacy records. These diverse sources are necessary given the nature of medications (e.g., multiple dosing and dose adjustments, particularly of insulin, for diabetes medication) [28,29].

· *Clinicians’ satisfaction.* Clinicians will complete a brief questionnaire after each encounter where we will ask about their satisfaction regarding the discussion they had with their patient about starting a medication.

· *Costs and resource utilization.* We will collect cost and utilization data from patients using two methods: first, by attempting to collect billing data from all clinicians the patient reports seeing in the six-month period and second, by collecting data on resource utilization from the patient questionnaire at six months. Data collected will include the number of hospitalizations, reason for hospitalization, whether the hospitalization was for medical or surgical condition, and the length of hospital stay. Additionally, we will collect data on emergency room and ambulatory care utilization. This utilization data will be costed according to the methods described by Glick et al. [30]. We will evaluate the economic impact of decision aid implementation from the clinician perspective based on the length of visits. The incremental time for decision aid visits will be considered the opportunity cost of using a decision aid. We will convert this incremental time to potential number of additional diabetes-related visits that could have been scheduled in 12-months in place of decision aid assisted visits. The visits will be costed using the Medicare Fee schedule for a diabetes-related visit. We will add the costs of materials (decision aids) to estimate the total practice-related costs.

To assess the *Reach* of the decision aids (**R**E-AIM), we will use a tracking log to record patients who are enrolled as well as those who declined the invitation to participate. We will use this data to evaluate reach, e.g., the ratio of enrolled patients to invited patients in each clinic and the characteristics of eligible patients who enrolled and declined. This will allow us to measure participation and representativeness.

To assess the *Adoption* of the decision aids (RE-**A**IM), we will estimate the proportion of practices or clinicians who adopt the intervention. Using clinician surveys and medical record review, we will compare the adoption rates across the intervention practices. We will select a random sample of medical records from each site to determine the extent to which the use of the decision aid is discernible in the records, and the extent of use and success when mentioned.

To assess the *Implementation* of the decision aids (RE-A**I**M), we will seek to determine the extent to which the intervention is implemented as intended. Using the video recordings of the clinical encounters, we will assess the fidelity with which the decision aids are delivered and used as intended during these clinical encounters. We have developed a fidelity checklist for each of the decision aids. These checklists have 10 to 12 items and are completed by a third observer reviewing the video recordings of the encounters [20].

To assess the *Maintenance* of the decision aids (RE-AI**M**), we will conduct a site visit and medical record review of eligible patients, approximately six months after removing investigator implementation support from the sites. This medical record review is in addition to the reviews that will take place at three and six months following the study visit.

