To evaluate the efficacy of the intervention, differences in all patient level outcomes, for both continuous and dichotomous outcomes (as well as patient characteristics at baseline) will be estimated using the random effects meta-analysis method [31]. This approach has been validated for matched pair cluster-based studies: differences in means for continuous outcomes and in proportions for dichotomous outcomes are estimated and then pooled across strata. A stratum in terms of a matched-pair study is considered to be each pair, and in this trial there are 5 strata. For each outcome, we will thus estimate the effect size and its precision (e.g., 95% confidence interval). The outcomes will be assessed at baseline, 3 and 6 months. We will estimate the intraclass correlation coefficient for each outcome along with its 95% confidence interval and report these for informational purposes only since the number of clusters is insufficient to determine with confidence a true intraclass correlation^124^. Within patients that had a diabetes medication discussion, HbA1c will be collected and categorized to <7.3 versus ≥7.3. This outcome will be analyzed as described above for categorical outcomes. All analysis and data management will be conducted utilizing SAS (version 9, Cary, NC) with use of Stata statistical software (version 11.0, College Station, Tx) for primary endpoint analysis.

Patients with missing outcome data will not be included in assessment of that particular outcome. We will compare the incidence of missing data for each outcome between study arms, both absolutely and as a function of follow-up period. We will report rates of missing data for each outcome by study arm and known reasons for missing data. In the event that the rate of missing data is not independent of study arm or is greater than the assumed 10% loss to follow-up, we will conduct sensitivity analyses under a range of assumptions about the missing values and assess consistency of results across those scenarios. In the event that patients are missing baseline characteristics data, which are otherwise imbalanced between the two study groups, we will use imputations to estimate models which include those characteristics.

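### Both stated sources for the secondary utilization and cost outcome depend on patient report, so events in patients who cannot or do not report may be lost, although record reviews are already planned

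*Protocol article*

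**What the plan says.** Resource utilization is a named secondary outcome under Outcomes measures. The paragraph on costs and resource utilization says that these data are collected from patients in two ways. The survey route works "by collecting data on resource utilization from the patient questionnaire at six months". The billing route, which the article lists ahead of it, works "by attempting to collect billing data from all clinicians the patient reports seeing in the six-month period". On content it says "Data collected will include the number of hospitalizations, reason for hospitalization, whether the hospitalization was for medical or surgical condition", with length of stay, and then "we will collect data on emergency room and ambulatory care utilization". The results are turned into costs.

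Three other places bear on this:
- The opening of Aim 1 names a second kind of patient data, "information about diabetes-related care included in medical records", and takes practice data from administrative and medical records.
- The paragraph on Maintenance describes a later record review that is "in addition to the reviews that will take place at three and six months following the study visit". Record reviews at three and six months are therefore already planned.
- The Analysis section says "Patients with missing outcome data will not be included in assessment of that particular outcome". It also commits to reporting missing data by arm with known reasons. Sensitivity analyses follow if missingness depends on arm or exceeds an assumed 10% loss to follow-up.

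**The concern.** For most outcomes in this trial, a missing form is a nuisance. For hospital and emergency use, the event being counted can itself be why the form is missing. The questionnaire needs a patient who is alive, well enough and willing to answer at six months. The billing route needs the patient to name the clinicians, and even then the bills are only sought. A patient who does neither has no stated route into this outcome, and the complete-case rule removes that patient.

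If such patients use more care than the others, rates and costs come out too low. If their share differs between arms, or if illness affects response differently in the two arms, the comparison is distorted as well. Costs are sensitive to this because a few admissions can dominate the total among 240 patients.

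Elsewhere the trial does not rely on the patient's answers in this way. Laboratory values, blood pressure and body mass index come from medical records, prescriptions come from pharmacy records, and adherence draws on several sources. Utilization has no stated source in the records.

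**Working it through.** **What there is to reproduce.** The plan gives no admission rate, no utilization rate and no power figure for this outcome. Its 80% power statement concerns a decision-quality score, and the primary outcome is collected immediately after the encounter, so neither is touched here.

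**Inputs from the document.** 240 patients (Sample size). Loss is given as 20% (Sample size) and as 10% (Analysis). Both are used below because the document gives both.

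**Inputs that are assumptions.** Six-month risk of at least one hospitalization in responders: 10%. Risk in non-responders: r = 2 or 3 times that. No event in a non-responder is recovered through billing or records.

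**Formula.** With loss d and observed risk p in responders, the true risk is (1 − d) × p + d × r × p = p × [1 + d(r − 1)].

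| Loss d | r | True risk | Reported risk | Rate understated by | Patients with an event who go uncounted |
|---|---|---|---|---|---|
| 20% | 2 | 8% + 4% = 12% | 10% | 1 − 10/12 = 17% | 4/12 = 33% |
| 20% | 3 | 8% + 6% = 14% | 10% | 1 − 10/14 = 29% | 6/14 = 43% |
| 10% | 2 | 9% + 2% = 11% | 10% | 1 − 10/11 = 9% | 2/11 = 18% |
| 10% | 3 | 9% + 3% = 12% | 10% | 1 − 10/12 = 17% | 3/12 = 25% |

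The last two columns answer different questions. The first is the error in the reported rate. The second is the share of affected patients who are never seen. At 20% loss, 0.20 × 240 = 48 patients would have no data, but only if billing yields nothing for any of them.

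**Cross-check from the other side.** Fix the true risk at h = 10% (24 of 240 patients) and let hospitalized patients be k times as likely not to respond. Non-response in those not hospitalized is d / (1 − h + hk), and in those hospitalized it is k times that, called d1. The observed risk is h(1 − d1)/(1 − d).
- d = 20%, k = 2: d1 = 2 × 0.20/1.1 = 0.364; observed 0.10 × 0.636/0.80 = 8.0%.
- d = 20%, k = 3: d1 = 3 × 0.20/1.2 = 0.50; observed 0.10 × 0.50/0.80 = 6.3%.
- d = 10%, k = 2 and 3: observed 9.1% and 8.3%.
- k = 1: observed 10.0% at either loss. Events are missed, but the rate is unbiased.

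**Between arms.** If d and r are the same in both arms, the bracket [1 + d(r − 1)] is the same and the ratio of rates is preserved. With r = 3 and loss of 15% in one arm and 25% in the other, equal observed rates of 10% correspond to true rates of 10% × 1.3 = 13% and 10% × 1.5 = 15%. For scale, the standard error of a difference between 13% and 15% with 120 per arm is √[(0.13 × 0.87 + 0.15 × 0.85)/120] = 4.5 points. With the plan's design effect of 1 + 29 × 0.05 = 2.45, it is 4.5 × √2.45 = 7.0 points.

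**The case against.** The strongest reply has four parts.

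*Billing is a real second source.* A reader might infer that these events are known only from what patients recall at six months. The article does not support that. Bills record the events themselves, the article does not say when patients name their clinicians, and the main diabetes clinician is known at enrolment. What stands is narrower: the search starts from the patient's report, and success is not assured.

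*The record reviews may already cover this.* The article does not list the abstracted fields, and its silence does not prove that admissions are excluded. But it does positively name the two utilization sources, and the record reviews are not among them. Patient record data are described as covering diabetes-related care, which need not include all admissions.

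*Missing data are handled.* The Analysis section does provide for sensitivity analyses, and 20% loss would trigger them. These vary assumptions about what was not seen. They do not retrieve an admission that may sit in a chart the team will be reading anyway.

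*The stakes are modest.* This is a secondary outcome in a trial whose abstract seeks a preliminary estimate, and the 2-point distortion above is small beside its standard error. That is fair and limits the weight of the point. It does not make an avoidable loss of events worth keeping.

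**Conclusion.** The point holds as a weakness in how a secondary outcome is ascertained. Both stated routes depend on patient report, patients without data are then excluded, and a less dependent source is already in the plan but not assigned to this outcome. Hospitalizations, emergency visits and costs may be understated, and the comparison may be biased if loss differs by arm.

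The documents cannot settle the size. Under the stated assumptions, a reported 10% stands against a true 12% to 14% at 20% loss, or 11% to 12% at 10% loss. Any recovery through billing shrinks the gap. If non-response is unrelated to illness, the rate is not biased.

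Two stronger readings should be resisted. One is that the sickest patients do drop out: this is a plausible risk, but no data in the article show who is lost. The other is that these are the only serious events the trial counts, making this a failure of safety reporting. The data are collected to measure utilization and cost, and a condensed article may leave adverse-event and death reporting to the full protocol.

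**What to change.** In the paragraph on costs and resource utilization, state that:
1. the medical record reviews already planned at three and six months, with the health system's administrative records where they hold such data, will record hospitalizations (reason and length of stay), emergency visits and ambulatory visits for every enrolled patient, whether or not the questionnaire is returned;
2. patient report and outside billing data will add care received elsewhere, under one written rule for combining sources and removing duplicates;
3. patients without a six-month form stay in the utilization analysis on their record data.

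The cost is a few more abstraction fields in reviews that already take place. The article does not say what the system's records hold on inpatient and emergency care, so this should be confirmed first. Care outside the system would still be known only through patient report. Repeating the utilization items in the existing three-month questionnaire would shorten recall, but it is optional because the article also aims to limit participant burden.
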